## Abstract

**Background:**

Neuropathic pain (NP) is one of the most frequent spinal cord injury (SCI) complications. Pain, quality of life, and functionality are associated and can lead to pain catastrophization. Pharmacological management of patients with NP secondary to SCI is widely known and there is increasing evidence in the area. Nevertheless, nonpharmacological management is not fully elucidated since its efficacy is inconclusive.

**Objective:**

We hypothesize that (1) hydrotherapy is effective in reducing NP secondary to SCI. Additionally, our secondary hypotheses are that (2) hydrotherapy decreases the catastrophization of NP, and that (3) hydrotherapy improves life quality and minimizes the degree of disability, when compared to physical therapy.

**Methods:**

A sample of approximately 20 participants will be randomly assigned to either the intervention (hydrotherapy) or control group (standard physical therapy). Both interventions will be administered twice a week over a 9-week period (18 sessions in total). Primary outcomes are changes in neuropathic pain perception and pain catastrophization. Secondary outcomes are changes in disability and quality of life scores. They will be assessed at baseline and follow-up at 4 weeks after discharge. Validated Spanish language scales that will be used are the following: Numerical Pain Rating Scale, Pain Catastrophization, Health-related Quality of life, and the World Health Organization’s Disability Assessment Schedule 2.0. Generalized mixed linear models will be used for comparing baseline and postintervention means of each group and their differences, together with 95% CIs and *P* values. A *P* value of less than .05 will be considered significant.

**Results:**

Recruitment began in April 2019, and we recruited the last participants by December 2019, with 10 individuals assigned to hydrotherapy and 8 to physical therapy (control). Results from this study will be disseminated via scientific publication, in ClinicalTrials.gov, and in national and international conferences in the latter half of 2022.

**Conclusions:**

This trial will explore the effects of hydrotherapy on neuropathic pain, together with functionality and quality of life, in patients with SCI. Furthermore, this study aims to evaluate these therapeutic modalities, including perception variables, and mental processes, which may affect the clinical condition and rehabilitation outcomes in these patients. Hydrotherapy is likely to be a safe, efficient, and cost-effective alternative to the current standard of care for NP secondary to SCI, with comparable results between the two.

**Trial Registration:**

ClinicalTrials.gov NCT04164810; https://clinicaltrials.gov/ct2/show/NCT04164810

**International Registered Report Identifier (IRRID):**

DERR1-10.2196/37255

## Introduction

### Background

Neuropathic pain (NP) is one of the most frequent spinal cord injury (SCI) complications, with the most negative impact on quality of life [1]. Patients with NP show significant differences in quality of life when compared to those without it [2]. The prevalence of NP secondary to SCI varies depending on the population characteristics, chronicity of the lesion, and the criteria of defining it. In a meta-analysis, the prevalence of NP in patients SCI was 53% (95% CI 38.58-67.47) [3], with a prevalence of 47.8% being observed in Cali, Colombia [4-6]. Pain, quality of life, and functionality are proven to be associated, and patients with secondary NP to SCI are affected in these areas [7,8], thus limiting participation in daily activities and self-care. Chronic pain has an effect on emotional state, as well as cognition, in regard to pain anticipation, which can further lead to catastrophization.

The term “pain catastrophization” is of a recent use, consisting of three components: rumination (putting excessive focus on the painful sensation), magnification (exaggerating the damage), and perception of inability to control the symptom [9]. Different strategies have been proposed to alleviate the complications of SCI [10-12]. The pharmacological management of patients with NP secondary to SCI is widely known, and there is increasing evidence of anticonvulsant and antidepressant use for its management [13,14]. Nevertheless, the nonpharmacological management is not fully elucidated since the efficacy is inconclusive. Previous studies reported interventions such as transcranial electrical stimulation, acupuncture, and transcutaneous electrical nerve stimulation [15,16], which improved NP in patients with SCI; however, more evidence on other nonpharmacological interventions is needed.

The physiological mechanisms of hydrotherapy on pain are well established [17,18], and there is evidence of its use in the management of painful syndromes such as fibromyalgia and chronic lower back pain [19-21]. In patients with multiple sclerosis, it has been found that hydrotherapy improves quality of life [22]; this also holds true for patients with mild Parkinson disease, where hydrotherapy had improvements on functional mobility [23,24]. Additionally, there have been registered improvements in active neck mobility in cases of cervical dystonia [25] and in postural balance of patients with stroke [26,27]. The effects of hydrotherapy in patients with NP secondary to SCI are currently unknown.

### Primary and Secondary Objectives

The main study hypothesis is that (1) hydrotherapy is effective in reducing NP in patients with SCI. Additionally, our secondary hypotheses are that (2) hydrotherapy decreases the catastrophization of neuropathic pain, and that (3) hydrotherapy improves life quality and minimizes the degree of disability, when compared to the other physical therapy techniques.

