### Assignment of Interventions

The groups compared in this study are the intervention (hydrotherapy) and control (standard physical therapy) groups. This control group was chosen as the current standard of care for nonpharmacological management of NP in SCI is physical therapy [30-32].

Participants will be assessed as follows: at the beginning of the intervention (baseline; Time 1) and at the end of the intervention (4 weeks after discharge; Time 2). Table 1 describes the schedule with procedures and the assessments scales in the trial timeline.

**Table 1 table1:** Schedule of enrollment and assessments.

Time point (T)		T1: baseline (week 0)	T2: follow-up (week 4)

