#### Effectiveness of the Intervention

Treatment effects will be derived using longitudinal modeling of within-person change in mean scores of the scales and subscales’ scores from baseline to follow-up. Baseline characteristics of participants in both groups will be compared using the chi-square or 2-tailed Fisher exact test for categorical variables, and the Student *t* test or Wilcoxon test for continuous variables, after assessing the tests’ assumptions. Statistical significance will be set at a 2-tailed α of .05, expressed as a 95% CI.

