## Discussion

### Expected Findings

The expected main findings of this study are as follows: (1) effects on minimizing disability and improving quality of life between current standard and novel hydrotherapeutic approach are comparable; (2) hydrotherapy is a safe, efficient, and effective alternative to the current management of NP secondary to SCI; (3) given a choice, patients are more likely to choose hydrotherapy rather than the current standard of care if both options are presented to them. To our best knowledge, this is the first trial that proposes to evaluate the effects of hydrotherapy in the NP reduction in Latin America.

The purpose of rehabilitation is to maximize patients’ daily functional independence through a goal-oriented treatment [55]. Heterogenous results from previous hydrotherapeutic studies on patients with diabetic or other metabolic neuropathies do not allow for definitive conclusions [56]. Conversely, the hydrotherapeutic approach for patients with peripheral neuropathies has yielded positive results on gait and balance, which, besides pain, are the most commonly presented symptoms in our patient cohort [6,57].

The presence of a control group is necessary, since there are no currently available nonpharmacological treatments with evidence for NP management in patients with SCI. The pilot trial design with parallel groups aims to provide preliminary evidence on the clinical efficacy of hydrotherapy on NP secondary to SCI, with a single-masked study design being performed in order to alleviate bias. Consideration of a DN-4 score of ≥4 out of 10 for the identification of NP and mixed pain syndromes [39] ensures adequate screening in our trial population. This questionnaire has been suggested for epidemiological studies, where accurate identification of NP symptoms is also crucial to test in order improve therapeutic approaches.

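### The main hypothesis names no comparator, and the between-arm contrast, though planned, is never made its test

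*Protocol article*

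**What the plan says.** Hypothesis 1 appears twice without a comparator. Under Primary and Secondary Objectives it reads "The main study hypothesis is that (1) hydrotherapy is effective in reducing NP in patients with SCI", and under Objective in the Abstract "We hypothesize that (1) hydrotherapy is effective in reducing NP secondary to SCI". The sentence ends there both times. A comparator appears only in the next sentence, which holds secondary hypotheses 2 (catastrophization) and 3 and closes with "hydrotherapy improves life quality and minimizes the degree of disability, when compared to the other physical therapy techniques".

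The analysis is described in three places:

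- Abstract, Methods: mixed models for "comparing baseline and postintervention means of each group and their differences, together with 95% CIs" and P values.
- Effectiveness of the Intervention: "Treatment effects will be derived using longitudinal modeling of within-person change in mean scores of the scales". The only group comparison named in that section is of baseline characteristics.
- Analysis of Outcomes: an intention-to-treat analysis by allocated arm, with a model for the effect of hydrotherapy whose named terms are time point and participant ID. No arm or arm-by-time term is named.

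Other sections do set up a comparison. Trial Design describes parallel groups allocated 1:1. Assignment of Interventions names hydrotherapy and standard physical therapy as the groups compared and justifies the control: "This control group was chosen as the current standard of care for nonpharmacological management of NP in SCI is physical therapy".

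On interpretation, Expected Findings anticipates that hydrotherapy will prove effective. The Conclusions, in the Abstract and in the Discussion, anticipate comparable results in the two arms. The Discussion's Conclusions leave superiority and noninferiority to later powered trials.

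**The concern.** A before-after fall in one arm is not a treatment effect. It also contains natural course, regression to the mean, the attention that comes with 18 sessions, and any concurrent pain medication or physical therapy, which the Interventions section permits in both groups. The randomised control arm exists to remove these components, and it does so only if the hypothesis is judged on the difference between arms.

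As worded, hypothesis 1 could be reported as met on the hydrotherapy arm's own P value. The article also expects hydrotherapy to be both effective and comparable to physical therapy. Similar falls in both arms could then be presented as confirming both, although such a result would not separate a treatment effect from the nonspecific components.

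**Working it through.** **The plan's own figure.** Sample Size and Power Calculation gives 20 participants, 10 per group, from pilot-study recommendations. No effect size, standard deviation or power is stated, so there is nothing to reproduce.

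**Inputs from the article.** Two-sided alpha is 0.05 (Effectiveness of the Intervention). The arms have 10 and 8 participants (Results).

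**Assumptions, not in the article.** Both arms have the same true mean improvement, d standard deviations of the change score, so the true between-arm difference is zero. Change scores are normal with equal variance. The range of d is 0.3 to 1.0. If the change SD on the 0-10 pain scale were 2 points, for illustration, d = 0.5 would be a 1-point fall and d = 1.0 a 2-point fall.

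**Within-arm test.** With two time points, the before-after comparison in one arm is represented by a paired t test. With falls counted as positive,

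P(significant fall) = 1 − F(t₀.₉₇₅,ₙ₋₁; n − 1, d√n),

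where F is the noncentral t distribution function. For hydrotherapy n = 10 and √10 = 3.162. For physical therapy n = 8.

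**Between-arm test.** In a two-sample t test on change, the shared improvement cancels. The test is therefore significant with probability 0.05 whatever d is, and 0.025 in favour of hydrotherapy. Simulation (200,000 trials each at d = 0.5, 0.8 and 1.0) gave 0.050, 0.049 and 0.049 in either direction, and about 0.025 in favour of hydrotherapy each time.

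| d | d√10 | Hydrotherapy fall significant (n = 10) | Physical therapy fall significant (n = 8) | Hydrotherapy significant, physical therapy not |
|---|---|---|---|---|
| 0.3 | 0.949 | 0.134 | 0.111 | 0.134 × 0.889 = 0.119 |
| 0.5 | 1.581 | 0.293 | 0.231 | 0.293 × 0.769 = 0.225 |
| 0.8 | 2.530 | 0.616 | 0.496 | 0.616 × 0.504 = 0.310 |
| 1.0 | 3.162 | 0.803 | 0.681 | 0.803 × 0.319 = 0.256 |

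The third column counts falls only, so its like-for-like comparison is 0.025. The usual 0.05 is the generous one.

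**The reverse error.** With 10 and 8 participants, a between-arm t test has power 0.168, 0.354 and 0.508 for true differences of 0.5, 0.8 and 1.0 SD of change. A nonsignificant difference in this pilot therefore says little about comparability.

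**The case against.** The strongest reply is that the comparison is already there. The Abstract's Methods include differences, Trial Design sets parallel groups, Assignment of Interventions names the two groups compared, and the analysis is by allocated arm. A reader might infer that the plan contains no between-arm test, or that it adopts a rule under which a within-arm P value settles efficacy. The documents support neither reading. What remains is narrower: no section says which contrast decides hypothesis 1.

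A reader might also infer that hypothesis 2 lacks a comparator. It shares a sentence with hypothesis 3, and the closing comparative phrase can govern both, so only hypothesis 1 is clearly without one.

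It is also tempting to argue that the control arm cannot help at all, because Expected Findings says "there are no currently available nonpharmacological treatments with evidence for NP management in patients with SCI". That is one Discussion sentence. The Background reports other nonpharmacological treatments that improved this pain, and physical therapy is presented elsewhere as standard care, with references that cannot be checked here. The point does not need this argument.

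On concurrent treatment, the Interventions section says it will be reported so that the analysis can allow for it. This reduces one component of a before-after change and leaves the others.

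A fuller protocol or analysis plan may name the decisive contrast, and the model description may be condensed. That is fair for the missing model term. It does not answer the hypothesis as worded, or the within-arm P values, both of which this article states.

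Finally, this is a pilot sized for recruitment feasibility, without power calculations. That lowers the severity. It does not remove the point, since the article still fixes an efficacy hypothesis and a significance level of .05.

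**Conclusion.** The point holds in limited form. The between-arm contrast is planned but is not made the test of the main hypothesis, and the wording leaves room to read a hydrotherapy-arm fall as effectiveness. With no true difference between arms, that reading would mislead in roughly 13% to 80% of trials for d from 0.3 to 1.0, against about 5% for the between-arm test.

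The range is illustrative. It rests on an assumed d and on paired t tests standing in for the planned mixed model. The 12% to 31% chance that hydrotherapy alone is significant matters only if someone draws a conclusion from that pattern, and no section proposes to. Because the trial is a feasibility-sized pilot that defers conclusive answers, this should be fixed but is not critical.

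**What to change.** - **Objectives (Abstract and Introduction):** state hypothesis 1 as a comparison of change in the Numerical Pain Rating Scale between hydrotherapy and standard physical therapy, and make clear that the same comparator applies to hypothesis 2. The wording must be reconciled with the expectation of comparable results and with the deferral of superiority and noninferiority.
- **Abstract Methods, Effectiveness of the Intervention, Analysis of Outcomes:** name the between-arm difference in change (the arm-by-time term) with its 95% CI as the only basis for a claim of effect. Report within-arm changes descriptively, without P values.
- **Abstract Conclusions, Expected Findings, Conclusions:** say that similar improvement in both arms, or a nonsignificant difference, will not be read as showing that hydrotherapy is effective or comparable.

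The cost is a few sentences and the loss of the within-arm P values. No new data are needed, and the change can be applied when the 18 participants are analysed and reported.

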## Methods

### Trial Design

We will carry out a single-masked pilot trial of parallel groups in usual clinical practice conditions, with an allocation ratio of 1:1 (SPIRIT checklist in Multimedia Appendix 1 and the World Health Organization’s Trial Registration Data Set in Multimedia Appendix 2).

### Participants

Participants will be recruited in two strategies: the first one involves screening eligible people in the SCI clinic in a prospective manner among those with appointments, and the second one involves calling participants in a follow-up call from the spinal cord service to check for their eligibility (Multimedia Appendix 3). Those eligible to participate in the study are patients who have a confirmed diagnosis of NP secondary to trauma in accordance with the International Spinal Cord Injury Pain classification [28], based on their clinical evaluation and physical examination, and those who meet the following criteria: ≥18 years of age, Douleur Neuropathique-4 (DN-4) score of ≥4 [29], and level of injury below C3. Exclusion criteria are as follows: active pressure ulcers, grade E of the American Spinal Cord Injury Association (ASIA) classification [28], cognitive impairment, ostomies, permanent bladder catheter, signs of systemic inflammatory response or urinary symptoms, major surgery in the past 2 months, noncontrolled hypertension (defined as a systolic blood pressure of >185 mm Hg or a diastolic blood pressure of >110 mm Hg refractory to treatment), active dyspeptic ulcer, severe liver fibrosis or portal hypertension, acute pericarditis or pancreatitis, known renal failure or requirement of hemodialysis or peritoneal dialysis, in-hospital stroke, and current participation in another clinical trial.

### Medical Assessment

The evaluation will begin with sociodemographic questions and presence of complications secondary to the SCI (participant questionnaire in Multimedia Appendix 4). In addition, the checklist of exclusion criteria for participation in the study will be verified (checklist of inclusion and exclusion criteria in Multimedia Appendix 5). In this initial evaluation, first measurement (baseline) will be performed. The medical examination will last 20 minutes and will be performed by a resident of the physical medicine and rehabilitation program. Once the medical evaluation is finished, the participants will be randomized into the control or intervention groups.

### Randomization

Participants will be assigned to one of the 2 groups by means of random blocks of 4, constructed with all possible combinations of the order of assignment based on random numbers (randomization protocol in Multimedia Appendix 6). The randomization list will remain with the coordinator for the whole duration of the study. Thus, randomization will be conducted without any influence of the principal investigators, interviewers, clinical evaluators, or therapists. The data analyst will be masked of participants’ allocation.

### Assignment of Interventions

The groups compared in this study are the intervention (hydrotherapy) and control (standard physical therapy) groups. This control group was chosen as the current standard of care for nonpharmacological management of NP in SCI is physical therapy [30-32].

Participants will be assessed as follows: at the beginning of the intervention (baseline; Time 1) and at the end of the intervention (4 weeks after discharge; Time 2). Table 1 describes the schedule with procedures and the assessments scales in the trial timeline.

**Table 1 table1:** Schedule of enrollment and assessments.

Time point (T)		T1: baseline (week 0)	T2: follow-up (week 4)
**Enrollment**			
	Project information: written or oral communication	✓	
	Written informed consent	✓	
	Eligibility assessment	✓	
	Randomization	✓	
**Assessment**			
	Douleur Neuropathique-4 items	✓	
**Primary outcomes**			
	Pain catastrophization Scale	✓	✓
	Numerical Pain Rating Scale	✓	✓
**Secondary outcomes**			
	Quality Short-Form Health Survey 36	✓	✓
	World Health Organization Disability Assessment Schedule 2.0	✓	✓

### Interventions

Participants in both groups will receive treatments twice a week for 9 weeks, resulting in a total of 18 sessions. Each session will last 1 hour. A 9-week period of interventions is considered because antidepressant and anticonvulsant drugs, which act on the intensity of neuropathic pain, cause effects after 3 weeks of administration. Since the pathophysiological mechanisms of interventions are similar [33], we are expecting to see initial effects only after this period. Additionally, previous studies with hydrotherapy and physical therapy also provided interventions in a 4-8–week period [34,35]. The second assessment has been scheduled 4 weeks after discharge since that time frame has proven as an adequate threshold for evaluating short-term training program efficacy in patients with SPI [30]. Participants will be scheduled for the therapy sessions and will be followed-up by a research coordinator who will remind the participants about their appointments.

The department of physical medicine and rehabilitation has 3 physical therapists specialized in hydrotherapy under different modalities, and a pool equipped to perform this type of intervention. The most commonly used techniques in the institution are Bad Ragaz [36] for motor control and the Watsu technique [37] for relaxation and spasticity management. The standard physical therapy protocol and the hydrotherapy protocol were reviewed by a panel of therapists and researchers. These protocols include technical and clinical adjustments to standardize therapeutic objectives of the interventions (standard physical therapy protocol in Multimedia Appendix 7 and the hydrotherapy protocol in Multimedia Appendix 8). Participants in any group can receive alternative treatments including medications for pain and physical therapy. They will inform researchers through the surveys and measurements of the study, so that the effects of those extra interventions in the analysis can be accounted for. Interventions will be discontinued if the participant requests it or owing to the appearance of exclusion criteria or severe adverse events (adverse event report form in Multimedia Appendix 9).

